### 2.4. Randomization

After evaluation of the inclusion and exclusion criteria, the participants eligible to participate in the study will be randomly separated into two groups: the control group (CG): which will have no activities performed; the experimental group (EG): which will follow the strength exercises protocol.

The randomization of the participants will be performed by an individual not directly related to the study. To avoid selection bias, random numbers will be generated by computer; the distribution will be made from a website: www.randomization.com. For the statistical analysis, the researcher in charge will receive the data without identifying the participants to obtain the results in a blinded manner. A randomization with a 1:1 computer-generated will be made for the group allocation.

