### 2.5. Data collection and procedures

The collection will take place in the facilities of the institutions related to fibromyalgia closest to the participants. If the volunteer cannot attend, the evaluation will be conducted in a public and neutral environment near the region where the research participant lives.

After the training period (8 weeks), the following week the participants of both EG and CG groups will be re-evaluated. From the 9th week on, the beginning of the off-training period will be accounted for, which will last 4 weeks. After this time, there will be a new reevaluation of both groups for future comparison. A schematic diagram of the schedule and steps is shown in Figure 2.

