### 2.9. Sample size calculation

The G-power software was used to detect a moderate effect size (partial eta squared of 0.09) in the intra/inter-group comparison. Considering an alpha value of 5%, the total number of participants should be 24 so that the power of the results is 90%. Considering a 20% of dropout risk, a minimum of 30 participants will be recruited (15 for each group).

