### 2.10. Statistical analysis

SPSS software will be used. To verify normality either the Shapiro-Wilk test (n < 30) will be used, and the equality of variances will be assessed by the Levene test. If the data, follow a normal distribution inter-group and intra-group differences will be calculated by repeated measures analysis of variance (ANOVA). If the data do not follow a normal distribution, the Kruskal-Wallis test will be calculated for between-group differences and the Friedman test for intra-group differences. To calculate the effect size, Cohen's test (intra-group comparison) will be used, and the between-group variance (partial eta squared) will be estimated. To verify the reliability of the tests and their measurements, the coefficient of variation and the intraclass correlation coefficient will be calculated. Finally, to evaluate the relationships between variables, Pearson's correlation coefficient will be calculated. The significance level will be set at 0.05.

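### Section 2.10 names partial eta squared as the only between-group effect size; at 24 to 30 participants it is biased upward, carries no direction or units, and is not produced by the plan's non-parametric branch

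*Protocol article*

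**What the plan says.** Section 2.10 sets out two branches. If the data are normal, a repeated-measures ANOVA is used for differences between and within groups. If not, Kruskal-Wallis is used between groups and Friedman within groups. One sentence on effect size follows, tied to neither branch: a Cohen measure for within-group change and, between groups, "the between-group variance (partial eta squared) will be estimated". No other between-group effect size is named. Testing is at the 0.05 level.

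Section 2.9 uses the same statistic as the design input: "The G-power software was used to detect a moderate effect size (partial eta squared of 0.09) in the intra/inter-group comparison". It continues: "Considering an alpha value of 5%, the total number of participants should be 24 so that the power of the results is 90", and "Considering a 20% of dropout risk, a minimum of 30 participants will be recruited (15 for each group". Section 2.4 gives 1:1 allocation. Section 2.5 has both groups measured again after training ("After the training period (8 weeks), the following week the participants of both EG and CG groups will be re-evaluated") and once more after the off-training period ("After this time, there will be a new reevaluation of both groups for future comparison"). With baseline, that makes three measurements.

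**The concern.** Partial eta squared is SS(effect) / [SS(effect) + SS(error)]. It is always at least zero, so chance differences between arms always add to it and never subtract. The smaller the trial, the larger that surplus, and this trial is small.

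Three further weaknesses come with the choice:

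- **Label.** The text calls it a between-group variance. It is a ratio of sums of squares.
- **No direction, no units.** The same value arises whether training helps or harms, and it cannot be read as FIQ-P points, centimetres of jump height or millimetres on a VAS.
- **Branch mismatch.** Kruskal-Wallis and Friedman are rank tests and do not produce it. For a non-normal outcome, the reported size would either come from an ANOVA that the plan has just set aside, or be missing.

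At stake is how readers judge the size of the training effect. The decision on whether an effect exists does not depend on it.

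**Working it through.** **Inputs.** Design effect 0.09, alpha 0.05, 24 completers and 30 recruited (section 2.9); two arms, 1:1 (section 2.4); three measurements (section 2.5, counting baseline). Assumed, because not stated: sphericity, and a correlation of 0.5 between repeated measurements for the sample-size check.

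**1. The plan's own figure.** f² = 0.09/0.91 = 0.0989. For the group-by-time test under the G*Power convention, λ = f² × N × m/(1 − ρ) = 0.0989 × 24 × 3/0.5 = 14.24, with 2 and 44 df. Power is 91.4%; with N = 22 it is 88.6%. So 24 reproduces, and 24/0.8 = 30.

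**2. Mean when there is no effect.** Partial eta squared then follows a Beta(df1/2, df2/2) distribution with mean df1/(df1 + df2).

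| | N = 24 | N = 30 |
|---|---|---|
| df, group | 1, 22 | 1, 28 |
| df, group-by-time | 2, 44 | 2, 56 |
| Null mean | 1/23 = 2/46 = 0.043 | 1/29 = 2/58 = 0.034 |
| Null median, group / group-by-time | 0.021 / 0.031 | 0.016 / 0.025 |
| P(estimate ≥ 0.09), group / group-by-time | 15.4% / 12.6% | 10.7% / 7.1% |
| Smallest estimate with p < 0.05, group / group-by-time | 0.164 / 0.127 | 0.130 / 0.102 |

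Relative to 0.09 the null means are 0.034/0.09 = 38% and 0.043/0.09 = 48%. A simulation of 40,000 trials agrees with the table. With sphericity violated, the group-by-time probabilities become 13.3% (N = 24) and 8.7% (N = 30).

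**3. What an observed 0.09 means.** F = (0.09/df1)/(0.91/df2) = 0.09/0.91 × 22 = 2.176 at N = 24, and likewise 2.176 on 2 and 44 df. The p-values are 0.154 and 0.126. At N = 30, F = 2.769 and p = 0.107 and 0.071. None is below 0.05.

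Bias-adjusted values for the group effect at N = 24:

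- epsilon squared = (F − 1)/(F + 22) = 1.176/24.176 = 0.049
- partial omega squared = (F − 1)/(F − 1 + 24) = 1.176/25.176 = 0.047

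At N = 30 both are about 0.06.

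**4. Mean when the true value is 0.09.** For the group effect, λ = N × 0.0989. Averaging over the noncentral F distribution gives 0.127 at N = 24 and 0.119 at N = 30. Epsilon squared averages about 0.083 to 0.088 in the same setting, close to the true value.

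**The case against.** The strongest reply is that this is a matter of convention. Partial eta squared is the usual companion to a repeated-measures ANOVA. Intervals, differences in original units and an effect size for the rank-test branch are details that an article may leave to a fuller document. No test result or sample size changes. Much of that stands, and the lack of a stated interval is not counted here as an error. What remains is that 2.10 does make a choice: it names one statistic, labels it wrongly, and applies it across both branches at a size where its bias is not negligible.

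A reader might also infer more than the article supports:

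- **That null effects will often look moderate.** For one outcome and one effect, 85 to 93% of null estimates fall below 0.09, and the median is 0.016 to 0.031. An estimate of exactly 0.09 would stand beside a non-significant p-value.
- **That results will be labelled moderate against 0.09.** Section 2.10 sets no size bands. The word belongs to the sample-size input in 2.9 ("to detect a moderate effect size (partial eta squared of 0.09").
- **That 0.09 is on the same scale as the values to be reported.** The figure of 24 reproduces only under a convention in which the design effect is about 14.24/(14.24 + 44) = 0.24 on the scale a repeated-measures ANOVA reports. Using 0.09 as a yardstick for reported values is therefore insecure.
- **That later trials will be sized from these estimates.** The Introduction speaks of reusing the protocol in future interventions, not of sizing trials from its effect estimates.

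The p-value is a real safeguard against reading noise as an effect, but it does not correct the reported size.

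**Conclusion.** The point holds as a small correction to the reported effect size and its label. At 24 to 30 participants, partial eta squared has a null mean of 0.034 to 0.043 and turns a true 0.09 into about 0.12 to 0.13 on average. It has no sign or units, is not a variance, and does not belong to the rank tests in the second branch. A null outcome reaches 0.09 in about 7 to 15% of cases.

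The figures assume equal arms, normal data, three measurements and, except in the sensitivity simulation, sphericity. The correlation of 0.5 matters only for reproducing the sample size. The planned tests, the sample size of 24 (30 recruited) and the main inference are unaffected.

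**What to change.** In section 2.10:

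1. Replace partial eta squared by partial omega squared or epsilon squared, with a confidence interval. Both are centred near zero when there is no effect.
2. Remove the description of the measure as between-group variance, and call it a proportion of variation.
3. For every outcome, in either branch, report the between-arm difference in the outcome's own units with its 95% interval. This supplies the direction and size that a proportion cannot, and gives the non-normal branch an effect estimate as well.

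The cost is a few sentences in 2.10 and a short script. No extra data, participants or tests are needed. The small downside is that the reported effect sizes become smaller: an observed 0.09 would appear as about 0.05 at N = 24 and about 0.06 at N = 30.

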## 3. Discussion

Since the last decade, has been a growing number of investigations related to fibromyalgia and specifically the relation of the syndrome with physical exercise (23, 32, 44, 45). Previous studies have already proven the effectiveness of different types of exercise on symptoms such as quality of life, anxiety, and balance, among other symptoms (21, 46). Despite such findings, most studies were conducted before the Covid-19 pandemic. The compliance rate for exercise by fibromyalgia patients before the pandemic was only 57.7% (47). During the social isolation caused by Covid-19, only 28.1% remained active during quarantine and the dropout rate of exercise programs was 46.7% (47). The lockdown had a negative impact on mental health and pain (48). The lack of motivation or worsening symptoms were already considered barriers to exercise before the pandemic (49). These factors were amplified during this time and could be related to the dropout or reduction of physical activity during this period. Furthermore, the impossibility of access to a specific place to perform physical activities during this time might have been another important contribution to dropout (47).

Given the aforementioned contextual changes, there is an urgent need for the encouragement of physical exercise, perhaps studying different forms of conducting and following physical exercise programs. Supervised online practice can be an interesting alternative as a form of support for these individuals. In addition, strength training ends up being less studied when compared to aerobic-type modalities, and more studies are needed in the area to obtain greater relevance as to its effect (14, 32). However, due to the pandemic, adaptations to intervention studies were necessary (50). Studies adapted virtual format have achieved positive results in disease impact with symptom reduction, proving to be effective and accessible (51, 52). Performing the interventions in real-time rather than pre-recorded videos may be a helping factor in avoiding the loss of research participants.

Another novelty of this protocol is the performance of strength exercises without the use of external materials and/or machines, using fewer repetitions per set than usual. This would probably allow the participant to perform each exercise without an excessive velocity loss in each set, enabling higher velocity stimulation and less fatigue per set (53). The high movement velocity and the low-velocity loss (few repetitions per set) are believed to stimulate the amount of force produced in little time, improving the neuromuscular response of the participants, and thus helping their functional capacity (54, 55). This decision goes differently from most of the exercise protocols found in the literature (14, 33).

A possible limitation of the study will be the participants' adherence due to the online intervention. Another limitation is the impossibility of blinding the instructor since it will be necessary to perform some evaluations. The results analysis will be done by another researcher, as informed in the methods to reduce the risk of bias.

Our protocol will provide an excellent strategy for application in new public health policies. Especially for communities and countries that seek to expand the reach of physical exercises as part of the treatment actions, focused on rheumatic diseases and specifically on FM. Physical Exercise is increasingly seen as a protective factor for health. This protocol increases the chances for this health service, with recognized benefits, reaching more people and groups with specific treatment needs and increasing accessibility, as in the case of our study. It will contribute to improving the cost-benefit ratio in the implementation of treatment. Furthermore, the knowledge obtained from the implementation of this protocol would allow a step forward on the possibility of designing a multicomponent training program including other types of training (e.g., aerobic and stretching) for this population.

It is important to highlight that the hybrid approach of this protocol constitutes the innovation of the investigation. The on-site evaluations will help complement the data for further support of the existing gap in the literature regarding balance and neuromuscular performance through a strength protocol. The online intervention will allow us to evaluate the participants' adherence and evolution regularly. It is expected to achieve positive results through a new approach to the strength training protocol that respects the limitations and individuality of the volunteers with adaptations of the exercises. Based on such results, the program will aim to increase independence by performing the exercises at home and perhaps contribute to sedentarism reduction. An exercise protocol that encourages the initiation of physical exercise is of utmost importance to assist in the management of fibromyalgia. Furthermore, the present protocol is easy to apply and has clear instructions and details related to exercise prescription.

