## 2. Materials and methods

### 2.1. Study design

The present study protocol refers to a single-blind, randomized controlled trial, developed according to Standard Protocol Items: Recommendations for Interventional Trials (SPIRIT) (34). The volunteers will be allocated randomly to the intervention group that will receive the exercise program or the control group. A staff member not involved in the study will be responsible for the randomization based on a computer-generated random number. The intervention program will last 12 weeks, consisting of 8 weeks of strength training plus 4 weeks of no training for the intervention group. The 1-month period will serve to evaluate how long the effects of the training will still be present after the training has ceased. The flow chart of the study design is represented in Figure 1.

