### 2.3. Research team

The research team will include 4 participants. Two researchers will be responsible for the evaluation of the groups—the control group and experimental group; one researcher responsible for the experimental group instruction; one staff member that is not related to the study to perform the randomization; one researcher will perform the data analysis.

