### 2.7. Intervention

#### 2.7.1. Experimental group

To include participants from all over the country, the training program will be carried out through real-time videos. The protocol consists of 8 weeks of training, consisting of 16 sessions of 50 mins, twice a week on alternate days. To facilitate follow-up during practice and reduce the risk of dropout, the volunteers will be divided into two groups with different times for each intervention. All volunteers will perform the exercise protocol at the meeting via an online (Google Meet platform) and both interventions will be performed during the same shift of the day. Each group will consist of 6 to 8 online participants. The sessions will be conducted and supervised by a physical therapist. Volunteers will be instructed about the exercises, protection and how to use the Borg scale at beginning of the meeting. During the meeting, before each exercise, the movement will first be demonstrated by the physical therapist, and then, sets and repetitions will be informed. To ensure that each participant will do the same number of sets and repetitions, all participants will perform the movement during the professional's count. This format will make it easier to count the rest time.

The program will consist of 10 mins of warm-up, 35 mins of strength exercises, and 5 mins of cool-down. The Borg scale will be used to monitor fatigue and perceived effort during practice (43). The protocol of the exercises to be performed during the training program, as well as their progression, are described in Tables 2, 3, respectively.

**Table 2 T2:** Description of strength training.

**Exercise**	**Name**	**Description**	**Position**	**Muscles**
Exercise 1	Sumô Box Squat	Stand near the chair with your feet wider than shoulder width. Start the movement standing with your hips and sit back. Be careful with the chest, knees, and shins.	Stand	**Primary:** Quadriceps. **Secondary:** Gluteus maximus, medius, and minimus; hamstrings, adductor magnus, longus, and brevis; erector spinae.
Exercise 2	T-exercise	From a standing position, bend at the hips and maintain a neutral spine. Perform dynamic motions by forming a T with the arms and return to starting position.	Stand	**Primary:** Lower and middle trapezius; rotator cuff musculature; posterior deltoid. **Secondary:** Hamstrings; gluteus maximus.

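### The Discussion implies that the unblinded instructor performs some evaluations, section 2.3 lists evaluators and instructor separately, and no assessor blinding is described in a trial labelled single-blind

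*Protocol article*

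**What the plan says.** Four places in the protocol article bear on who measures outcomes and who is blinded.

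- **Section 2.1 (Study design):** "The present study protocol refers to a single-blind, randomized controlled trial". The blinded party is not named there.
- **Section 2.3 (Research team):** "Two researchers will be responsible for the evaluation of the groups", and, as a separate entry, "one researcher responsible for the experimental group instruction". The list also has a staff member for randomization and a researcher for data analysis.
- **Section 2.4 (Randomization):** the researcher in charge of the statistical analysis "will receive the data without identifying the participants to obtain the results in a blinded manner".
- **Section 3 (Discussion), on limitations:** "Another limitation is the impossibility of blinding the instructor since it will be necessary to perform some evaluations". The next sentence gives the safeguard: "The results analysis will be done by another researcher, as informed in the methods to reduce the risk of bias".

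Section 2.7.1 adds who delivers the intervention: "The sessions will be conducted and supervised by a physical therapist". That person necessarily knows who is in the experimental group.

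**The concern.** Sections 2.3 and 3 do not fit together. Section 2.3 keeps evaluation and instruction apart. The Discussion gives the need to perform evaluations as the reason the instructor cannot be blinded, which suggests that the two roles overlap.

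The controls receive no activity, so participants know their arm and cannot be blinded. Assessor blinding is then the available safeguard for outcomes that an assessor administers. Balance and neuromuscular performance are both in the stated aim, and they are measured by such tests. Someone who has coached one arm live for up to 16 sessions may instruct or encourage that arm differently from controls met only for testing. The article describes no protection at that step.

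**Working it through.** No figure in the plan is at issue, so the check sets the passages side by side.

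**1. Who evaluates, by section 2.3.** Two researchers evaluate and one instructs, listed as different roles. The section says "The research team will include 4 participants". The roles listed are 2 evaluators + 1 instructor + 1 randomization staff member + 1 analyst = 5.
- If the staff member, described as unrelated to the study, is not counted, 5 − 1 = 4. Every role then has its own person, and the instructor does not evaluate.
- If the staff member is counted, five roles are shared by four people. Someone holds two, and the text does not say who.

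The count therefore does not settle the question.

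**2. Who evaluates, by the Discussion.** The instructor is the only person named in the limitation sentence. The reason given for not blinding the instructor is that evaluations must be performed. The following sentence assigns the analysis to another researcher, as a contrast with that person. Together the two sentences point to an instructor who also evaluates. This is an inference: the verb has no stated subject and the evaluations are not specified.

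**3. Who is blinded.** Section 2.1 makes the claim without naming anyone. Section 2.4 blinds the analyst. Nothing says that the two evaluators are unaware of allocation or that the instructor is kept out of outcome assessment. The safeguard in the Discussion is again the separate analyst. It acts after the data exist and cannot undo a difference introduced at measurement.

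**4. Which outcomes are exposed.**
- *Vertical jump and medicine ball throw (2.6.4):* three attempts each. Jumpers are told to go as high and as fast as they can. Effort can respond to how the instruction is given.
- *Balance (2.6.5):* a force plate records the result, but an assessor sets up and instructs the three conditions.
- *FIQ-P and VAS, including the daily app entries (2.6.1 to 2.6.3):* self-reported by participants who know their arm. Changing the assessor helps little here.

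**5. Size.** The article gives no estimate of assessor bias and does not say how many evaluations the instructor would perform. No magnitude follows from it.

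**The case against.** The strongest reply is that section 2.3, in the Methods, is the operative text and already separates the roles, and that the conflict comes from one loosely worded limitation. The sentence is odd in itself, because an instructor is unblinded by teaching the experimental group whether or not any evaluation follows. The evaluations could be those made within sessions: effort on the Borg scale (2.7.1), attention to pain (2.8), or the regular follow-up of adherence and progress mentioned in the Discussion. This stands in part. It rules out saying that the protocol assigns outcome measurement to the instructor. It does not remove the problem, because in-session monitoring would not explain a limitation on blinding, and on any reading the evaluators' blinding is not described.

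It is also fair that optical timing and a force plate give objective readings. They do not standardize the instruction or effort behind those readings.

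Three stronger readings are tempting, and the document does not support them.

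- *One evaluator per arm.* A reader might infer this from section 2.3. The natural sense is that both researchers evaluate both groups, and nothing indicates a split.
- *The analyst is not blinded.* Removing participant identities does not by itself hide the arm. But section 2.4 states the aim of blinded analysis, and an article may leave the masking method to the full protocol. It is worth a clarifying phrase, not a finding of its own.
- *A quantified false-positive rate.* With a two-sample t test, 12 per arm (24 / 2) and two-sided 5%, the result depends wholly on the bias assumed: a spurious shift of 0.1 to 0.2 SD gives rejection rates of 5.6% to 7.6%, and 0.3 to 0.5 SD gives 10.8% to 21.6%. Nothing in the article supports any of these shifts, and its planned analysis is repeated-measures ANOVA. The figures show the sensitivity but do not measure the problem.

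**Conclusion.** The point holds as an inconsistency with a real consequence for bias. The Discussion most plainly implies that the unblinded instructor performs some evaluations, section 2.3 lists separate evaluators, and the only blinding described is at the analysis stage. The protection that the single-blind label suggests is therefore not shown for the jump, throw and balance tests.

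The conclusion assumes that the evaluations in the Discussion include outcome assessments, which is a strong inference and not a literal statement. If they are only in-session monitoring, the remaining gap is that the article describes no blinding of the evaluators and does not say whom single-blind covers. The size of any bias cannot be derived from the document. The point does not extend with the same force to the self-reported outcomes.

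**What to change.** Reconcile section 2.3 and the Discussion before outcome data are collected:

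1. State in section 2.3 that the instructor performs no outcome assessment. The two evaluators already on the team do all of them, each for participants from both arms, without being told the allocation and with a standard instruction script.
2. State in section 2.1 whom single-blind covers.
3. State in section 2.4 that the analyst receives coded arms.
4. Reword the Discussion limitation to match what is done: the instructor and the participants cannot be blinded, so the self-reported outcomes remain open to bias. Do not delete it, since that would only remove a disclosed limitation.

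If the instructor must perform some outcome assessments, name them and report them as unblinded.

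Cost: no new staff, because both evaluators are already listed. Some scheduling effort is needed, because assessments take place at sites near the participants (section 2.5) and recruitment is nationwide (section 2.7.1). The article does not allow that effort to be quantified.
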